### 7.2.2 CD4+ count

CD4+ counts will be measured at the local site laboratory using the standard flow cytometry method used by the site. The site laboratory will be required to demonstrate satisfactory participation in a recognised quality control programme for CD4+ count testing.

### 7.2.3 Resistance testing

Drug resistance is the key component of the primary endpoint, and hence the detection of new resistance mutations needs to be pursued fastidiously in this trial.

All patients who have a VL rebound confirmation sample taken will have a number of additional blood samples drawn at the same time (see section 7.1.6), including a sample for storage for local genotypic resistance testing. Genotypic resistance testing will be performed on the sample if the VL confirmation result is  $\geq 50$  copies/ml. Resistance testing will be performed by the local laboratory that is normally used by the site. A designated referral laboratory, normally used by the site for performing resistance testing at low VL levels, may be used also. In the event that sequencing is unsuccessful, the sample stored for genotypic resistance testing will be transferred to the PIVOT storage samples and will be tested by the study central resistance laboratory at UCL/UCLH at the end of the study period. All the sequences will be analysed using the Stanford algorithm, and the level of resistance to individual drugs will be classified as none (susceptible), potential low level, low level, intermediate level, high level.

Comparison will be made with the drug resistance profile obtained from any other previous sequences available for that patient (pre-treatment resistance testing is commonly performed at most centres in the UK). If a patient develops virological rebound with resistance during the course of the trial but does not have a prior resistance test result for comparison, attempts will be made to identify a stored (pre-treatment) sample and if

available this sample will be tested to determine whether transmitted resistance was present prior to antiretroviral therapy.

As a further measure to make the best possible comparison of the two treatment strategies in terms of drug resistance development, selected stored samples from patients who have rebounded to a sufficiently high viral load (VL > 1000 copies/ml) will be tested using a minority species resistance assay at the end of the trial.

#### **7.2.4 Quality of Life (QoL) assessment**

This will be assessed using the Medical Outcomes Study HIV Health Survey (MOS-HIV), a 30-item QoL questionnaire based on the SF36 which has been validated for use in patients with HIV infection (22) (see Appendix 6). The questionnaire takes about 5 minutes for patients to self-complete, and this will be done at baseline, at 12 weeks, and annually during the trial.

#### **7.2.5 Neurocognitive assessment**

Neurocognitive function will be assessed at Baseline, Week 12, annual visits and the final trial visit using a series of simple neuropsychological tests that can be administered by a clinician or research nurse without specific neuropsychological training, and that will take about 20 minutes to perform. The most common neurocognitive impairments seen in HIV-infected individuals are those that affect frontal sub-cortical functions (23-25). Therefore, the tests have been chosen to detect changes in these functions such as psychomotor speed, memory, executive functions (e.g. processing instructions) and fine motor speed. The following simple, well-established tests will be performed (details provided in Appendix 13):

- Hopkins Verbal Learning Test - Revised. This assesses verbal learning and memory. The examiner reads 12 words and the participant is asked to recall them immediately. The exercise is performed a further two times in exactly the same way. The free recall trials are followed by a recognition test where the examiner reads aloud a list of 24 words and the participant must answer yes or no for each of them depending if the word was or was not included in the original list of 12 words. Finally, after performing the remaining tests listed below and completing the MOS-HIV quality of life questionnaire (i.e. after about 15-20 minutes), the initial free recall test is repeated (without the examiner repeating the list again) to assess delayed memory. A final score based on the number of words recalled or recognised in each part of the test will be calculated (a separate score for immediate and for delayed memory will be produced).
- Colour trails tests (two parts). These assess psychomotor speed and cognitive flexibility within the executive functioning domain (26). In Part 1, participants will be asked to connect a series of encircled numbers in numerical order. In Part 2 they will be also asked to connect 25 encircled numbers alternating between two colours. The score is the time to completion of each of the tasks.
- Grooved Pegboard test. This assesses psychomotor speed and fine motor function. It is a manipulative dexterity test consisting of 25 holes with randomly positioned slots. Pegs have a key along one side and they must be rotated to match the hole before they can be inserted. Participants are asked to insert the pegs into the slots as rapidly as possible, and the test will be performed with both the dominant and the non-dominant hand. The score is the time to completion of the task (each hand scored separately).

The participant will be given their raw test scores if so desired. The investigator will be provided with a table of normal ranges for each of the tests based on standard population data so that some interpretation of the participant's score can be made, if the participant wishes results to be expressed in that way.

The final evaluation of each participant's neurocognitive function will be done centrally to calculate a neurocognitive function summary score, as described in section 9.5.2.

## 7.3 Procedures for assessing safety

A symptom evaluation and targeted physical examination will be performed at each visit.

Body composition changes will be evaluated at baseline, annual visits and the final study visit as follows:

- Waist circumference will be measured between the lower border of the ribs and the iliac crest, in a horizontal plane.
- Hip circumference will be measured at the widest point over the buttocks.
- Patients will be asked about any change in fat in the face, arms, legs or abdomen. Taking into account the patient's opinion, the research nurse or doctor will grade facial lipoatrophy as none, moderate (evident on inspection), or severe (immediately obvious).

Patients will be asked about symptoms of peripheral neuropathy at baseline, annual visits and the final study visit. A brief neuropathy examination will be performed at baseline and the final study visit in all patients, and at intervening annual study visits if the patient reports neuropathy symptoms

Cardiovascular risk factors will be assessed at annual trial visits, and risk will be quantified using the Joint British Societies cardiovascular risk prediction charts (see Appendix 11).

Blood will be drawn at trial visits to assess laboratory safety parameters according to standard-of-care as indicated in the schedule of trial assessments (see section 1.3). Additional safety blood tests or investigations will be performed to investigate symptoms or monitor emergent laboratory test abnormalities as clinically indicated.

All adverse events will be reported on the case report form. Adverse events (clinical and laboratory) will be graded using the 2004 Division of AIDS toxicity grading scale (see Appendix 7). Serious adverse events will be defined according to the EU Directive 2001/20/EC Article 2 based on ICH GCP, and will be reported to the MRC CTU for the duration of the main trial i.e. whilst patients are attending trial visits according to standard timelines (see section 11).

Diagnostic criteria for selected serious AIDS and non-AIDS events are defined in the protocol (see section 9.2.2 and Appendices 8 and 9), and sites will be encouraged to investigate patients in a way that allows determination of whether patients meet the specified diagnostic criteria. An independent endpoint review committee will review these endpoints to ensure that they satisfy the criteria.

### 7.3.1 Procedures for Therapeutic Drug Monitoring

Patients in the PI monotherapy arm will have a blood sample taken at Week 4 for measurement of PI concentration. The sample should be a trough sample (i.e. taken at the time when the next dose of medication would ordinarily be due) if at all possible, or obtained at the very least 4 hours following the last dose. The time of the last dose of PI taken will be recorded. If the PI concentration is low at week 4, then the test may be repeated at week 8 and/or week 12, at the clinician's discretion. A blood sample for PI concentration will also be

taken at 4 weeks after any change in PI drug in patients on PI monotherapy to ensure that adequate concentrations are attained with the new drug. If the levels are low, this may also be repeated at 8 weeks or 12 weeks following the introduction of the new PI (at the clinician's discretion).

Samples will be sent from sites using the normal procedures for dispatching samples for therapeutic drug monitoring which is performed in the UK by Delphic Diagnostics. Results will be made available to the sites within approximately 2 weeks of sample collection. When a trough sample was not available, population pharmacokinetic data will be used to predict the trough level. Advice on whether dose modification of the PI may be indicated will be provided with the result.

PI concentration may also be measured in patients who have a confirmed VL rebound, to assist with the interpretation of the causes of rebound. These samples may be stored for later testing in batches. The results will not be essential for clinical care because the patient will have switched back to triple-therapy. The results will be reported to the treating clinician but this may not be in real time.

## **7.4 Procedures for assessing health economics**

The trial will measure all the costs (from an NHS perspective) of participants in the trial regardless of why costs were incurred throughout the trial. Data on service receipt (resource utilisation) will be collected at each trial visit by asking patients about visits to HIV clinics, outpatient (non-HIV) clinics, A&E departments or GPs, days off work due to illness, and any periods of hospitalisation since the previous documented trial visit. The duration of hospitalisation and main diagnosis will be recorded (verified if possible by reference to a hospital discharge summary). Patients will complete the EQ-5D questionnaire (see Appendix 5) at each trial visit to permit cost-utility analysis (27).

## **7.5 Trial closure**

All patients will be followed according to the trial schedule until a common trial closing date. The trial will be closed after completion of the extension phase and all data queries have been resolved.

## **8. LOSS TO FOLLOW-UP & WITHDRAWAL**

### **8.1 Patient transfers**

For patients moving from the clinical site, every effort should be made for the patient to be followed-up at another participating trial centre and for this trial centre to take over responsibility for the patient. MRC CTU should be informed and a copy of the patient CRFs will need to be provided to the new site. The patient will have to sign a consent form at the new site, and until this occurs, the patient remains the responsibility of the original centre.

### **8.2 Loss to follow-up**

A patient will be regarded as 'lost to follow-up' if they have not been seen in clinic for more than 8 months. After this time, a check will be performed through disease databases or death registers (e.g. Office for National Statistics, CDSC Colindale). Consent will be obtained for this when the patient enters the trial (see Appendix 2). Subsequently, if the patient attends clinic and a CRF is received by the MRC CTU, the 'lost to follow-up' status will be reversed.

### **8.3 Withdrawal of consent**

In consenting to the trial, patients are consenting to treatment according to the allocated treatment strategy as well as to trial follow-up visits and data collection. If a patient wishes to withdraw from the trial treatment strategy, the doctor/nurse will explain the importance of remaining on trial follow-up or, failing this, of allowing routine clinic follow-up data to be used for trial purposes.

If the patient explicitly states their wish not to contribute further data to the trial, the trial doctor should inform the MRC CTU in writing (i.e. a withdrawal CRF should be completed). Data up to the point of withdrawal can be included in the analysis. Further data i.e. vital status can only be obtained through NHS databases and registers (as above).

## 9. STATISTICAL CONSIDERATIONS

### 9.1 Method of randomisation

Patients will be randomised using a computer-generated algorithm based on random permuted blocks.

### 9.2 Outcome measures

Analyses will compare the PI monotherapy and standard treatment arms on the following outcome measures:

#### 9.2.1 Primary outcome measure

- **Loss of future drug options**

Defined as the first occurrence of intermediate to high level resistance to any one or more of the standard antiretroviral drugs (limited to licensed drugs in contemporary use) to which the patient's virus was considered to be sensitive at trial entry (i.e. excluding drug resistance that was known to be present on previous resistance testing).

#### 9.2.2 Secondary outcome measures

- **Serious drug or disease-related complication**

Defined as the first occurrence of one of the following in any individual patient:

- **Death from any cause**
- **Serious AIDS-defining illness** (see diagnostic criteria, Appendix 7)
- **Serious non-AIDS defining illness** (see diagnostic criteria, Appendix 8)
  - Acute myocardial infarction
  - Coronary artery disease requiring invasive procedures
  - Cirrhosis
  - Acute liver failure
  - End-stage renal disease
  - Stroke
  - Clinical acute pancreatitis
  - Severe lactic acidemia
  - Severe facial lipoatrophy
  - Severe peripheral neuropathy
  - Non-AIDS malignancy

- **Adverse events**

Defined as the total number of Grade III and IV adverse events.

- **Confirmed Virological rebound**

Defined as 3 consecutive VL tests  $\geq 50$  copies/ml, with at least 4 weeks between the first and last test. One of these 3 tests may be a repeat of the same sample. There are a number of alternative definitions for virological rebound, each of which has advantages and limitations (28). The alternative definitions to be used in this trial will be described in the full statistical analysis plan.

- **CD4+ count change**  
Defined as change from baseline in absolute CD4+ count.
- **Health-related Quality of Life change**  
Defined as change from baseline in the mental and physical health summary scores.
- **Neurocognitive function change**  
Defined as change from baseline in the neurocognitive function summary score.
- **Cardiovascular risk change**  
Defined as change from baseline in the risk of cardiovascular disease calculated from the Framingham equation (19).
- **Health care costs**  
Defined as the total cost of health care resources utilised per patient year.

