### 4.1 Patient inclusion criteria

1. Documented HIV infection on ELISA and confirmatory test.
2. Male or female patients, aged 18 years or more.
3. Receiving combination ART for at least 24 weeks with a regimen comprising 2 NRTIs and either an NNRTI or a PI (boosted or un-boosted).
4. No change in ART drugs in the 12 weeks prior to screening.
5. Plasma VL <50 copies/ml at screening and for at least 24 weeks prior to screening (must have at least 1 documented result <50 copies/ml at more than 24 weeks prior to screening, and at least 1 documented result <50 copies/ml taken within 24 weeks prior to screening). A patient who has had one VL "blip" to <200 copies/ml in the 24 weeks prior to screening may be included, provided that the 2 VL tests that immediately preceded the blip and all VL tests (of which there must be at least 1 prior to screening) that immediately followed the blip all gave results <50 copies/ml.
6. CD4+ count >100 cells/mm^3 at screening.  
*This criterion is included because immune reconstitution is a priority in patients with very low CD4+ counts, and there is currently insufficient data to assess whether PI monotherapy will lead to equivalent rates of CD4+ recovery as standard-of-care treatment.*
7. Willing to continue unchanged or to modify, antiretroviral therapy, in accordance with the randomised assignment.
8. Likely to be resident in the UK for the full duration of the trial and willing to comply with trial visit schedule throughout the follow-up period.
9. Willing to provide written informed consent.

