## 5. RANDOMISATION & ENROLMENT

### 5.1 Randomisation visit (Baseline; Day 0)

If at all possible, the randomisation visit should occur within 4 weeks following the screening visit, but this may be extended to a maximum of 8 weeks for reasons of patient convenience or other operational reasons. The results of all the screening assessments (including ECG) must be available prior to randomisation. There is no requirement for fasting at this trial visit.

For trial entry, all eligibility criteria must be fulfilled. These include the results of the evaluations carried out at screening which must be reviewed prior to the randomisation to make sure that the patient meets the criteria for trial entry. The research team should confirm that the patient continues to consent to enter the trial. The patient will be advised to inform their general practitioner of their trial participation, but this will not be a pre-requisite to enrolment. If the patient consents for their GP to be informed about participation (see Appendix 2) a letter should be sent to the GP (see Appendix 3).

Baseline assessments will be performed as listed below and as summarised in the Trial Schedule (see section 1.3).

- Review of medical and drug history since the screening visit
- Review of symptoms
- Review of concomitant medications
- Adherence to ART (patient will be asked about the number of missed doses in the previous 2 weeks, and in the previous 3 months)
- Targeted physical examination (as needed to evaluate symptoms; at this visit will include measurement of blood pressure, body weight, waist and hip-circumference, assessment of facial lipoatrophy and peripheral neuropathy)
- Neurocognitive assessment
- MOS-HIV quality of life questionnaire (self-completed by patient)
- EQ-5D health status questionnaire (self-completed by patient)
- Laboratory tests:
  - HIV viral load
  - CD4+ count
  - Full blood count (haemoglobin, white cells, neutrophils, lymphocytes and platelets)
  - Biochemistry (sodium, potassium, urea, creatinine, bilirubin, ALT, alkaline phosphatase)
  - Plasma storage (1 X 4ml EDTA tube)

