## **6.5 Management of cardiovascular disease risk factors**

Cardiovascular risk factors (smoking status, blood pressure, fasting serum lipids and glucose) will be evaluated at baseline and annually during the trial.

At each of these annual assessments patients who report that they continue to smoke will be advised to give up smoking. This should be particularly emphasised in patients who have other factors that elevate cardiovascular risk. Patients who indicate that they are willing to attempt to stop smoking will be provided with contacts for smoking cessation programmes, or other counselling and assistance as appropriate.

Elevated blood pressure will be managed according to standard treatment guidelines.

Elevated lipid levels will be evaluated according to standard thresholds for treatment and managed according to current treatment guidelines. Management decisions should be based on fasted results. If elevated triglyceride or cholesterol results are obtained from a non-fasting blood sample, the test should be repeated after an overnight (minimum 8-hour) fast before management changes are instigated. Management will initially involve counselling to make appropriate changes in diet and exercise routine. Subsequently, if indicated, anti-hyperlipidaemia medication may be used. If treatment with a statin is indicated, a drug that is not metabolised by the CYP3A4 pathway should be prescribed e.g. pravastatin (but consider possible interaction with darunavir), atorvastatin, or rosuvastatin (but consider possible interaction with lopinavir or darunavir). Up-to-date information on drug interactions should be sought (see reference sources in section 6.6, below). If these measures fail to provide adequate control of lipids, changes in ART may be considered (e.g. switching to an alternative PI or NNRTI that is considered to be less prone to cause hyperlipidaemia). Every attempt should be made to maintain the patient within the allocated treatment strategy and consideration should be given to discontinuing a PI only if lipid levels cannot be adequately controlled with these measures.

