## 9.5 Analysis plan

A full statistical analysis plan will be developed before the trial is analysed. It will be based on the following summary:

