### 9.5.2 Secondary analyses

The primary analysis will be extended to tabulate individual ART drug options and ART class options which are lost due to the development of resistance. Time-to-event methods will be used to analyse the rate of serious drug- or disease-related complications and for viral load rebound. Also, the frequency of grade III and IV adverse events will be tabulated by body systems and randomised group and the groups will be compared using the  $\chi^2$  test. Repeated measures analysis will be used to compare change in CD4+ cell count from baseline in the allocated strategies.

Patient responses on the MOS-HIV questionnaire will be converted to scores on 11 subscales, ranging from 0 to 100, with higher scores indicating better health (32). The scores are then synthesised into a physical health summary score (PHS) and a mental health summary score (MHS). A general linear mixed model will be used to compare the two groups in terms of changes from baseline in the summary PHS and MHS quality of life indexes over the follow-up period.

The scores on each of the neurocognitive tests will be standardised using demographic-adjusted normative means. This procedure will adjust the data for gender, age, level of education and ethnic background. Briefly, standard scores will be calculated by subtracting the appropriate normative mean from the raw score and then dividing by the appropriate normative standard deviation to give a z score (33). The patient's individual z scores on each test will be averaged to give the patient's neurocognitive function summary score at each

visit. A general linear mixed model will be used to compare the two groups in terms of changes from baseline in the neurocognitive function summary score.

Changes from baseline in the 10-year cardiovascular risk score will also be compared between the two groups using a general linear mixed model.

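### Baseline CD4 is, on the natural reading, the single Day 0 count; averaging it with the screening count would make this secondary outcome more precise at no cost

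*Combined protocol and SAP*

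**What the plan says.** The secondary outcome in section 9.2.2 is "Defined as change from baseline in absolute CD4+ count". Section 9.5.2 adds the method: "Repeated measures analysis will be used to compare change in CD4+ cell count from baseline in the allocated strategies". Neither section says which pre-treatment count is the baseline, or whether the model adjusts for it.

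Two counts are available. CD4 is among the screening laboratory tests (section 4.3.2) and the Day 0 tests (section 5.1), and the schedule in section 1.3 marks both. The heading of section 5.1 and the Day 0 column of the schedule call the randomisation visit the baseline.

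The two counts are close in time and precede any trial-driven change of drugs. Inclusion criterion 4 requires "No change in ART drugs in the 12 weeks prior to screening". Randomisation should come "within 4 weeks following the screening visit, but this may be extended to a maximum of 8 weeks". In the monotherapy arm, drugs change only on or after randomisation (section 6.3.1).

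Section 9.5 is a summary: "A full statistical analysis plan will be developed before the trial is analysed".

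**The concern.** A single CD4 count is a noisy measure of a patient's level. A change score carries the whole error of its baseline count into every follow-up comparison, however many follow-up counts there are. With 12-weekly counts, 13 are due by week 156. If change is summarised over those 13, the single baseline count accounts for 1/(1 + 1/13) = 93% of the measurement error in the change. A second count of the same quantity is already held and, on the natural reading, unused.

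What is at stake is precision on one secondary outcome. That outcome has some weight: the note to inclusion criterion 6 says it is not yet known whether CD4 recovery on PI monotherapy matches standard care.

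**Working it through.** **What can be reproduced.** The plan gives no SD, correlation, target difference or power for CD4, so there is no figure of its own to check. The sample size in section 9.3 rests on the resistance endpoint.

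**Inputs.** From the documents: two pre-treatment counts, at most 8 weeks apart, and 12-weekly follow-up counts (13 by week 156). Assumed: within-patient SD sw = 80 to 120 cells; SD of true change sd = 100 to 150; between-patient SD sb = 200 to 220; within-patient deviations independent between visits.

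**Formulas**, with m baseline counts and k follow-up counts:

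- Raw change: variance = sw²(1/m + 1/k) + sd²
- Baseline-adjusted: residual variance = sb² + sd² + sw²/k − sb⁴/(sb² + sw²/m)

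**Central case**, sw = 100, sd = 100, sb = 200, k = 13:

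- Raw, m = 1: 10,000 × 1.0769 + 10,000 = 20,769. Raw, m = 2: 10,000 × 0.5769 + 10,000 = 15,769. Saving 5,000/20,769 = 24%.
- Adjusted, m = 1: 50,769 − 1.6×10⁹/50,000 = 18,769. Adjusted, m = 2: 50,769 − 1.6×10⁹/45,000 = 15,214. Saving 3,556/18,769 = 19%.

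**Extremes, mean of 13 counts:**

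- Raw, low (sw 80, sd 150): 3,200/29,392 = 10.9%. High (sw 120, sd 100): 7,200/25,508 = 28.2%.
- Adjusted, low (80, 150, sb 200): 2,554/28,510 = 9.0%. High (120, 100, sb 220): 4,831/22,206 = 21.8%.

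**Change at a single visit, k = 1:**

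- Raw: low 3,200/35,300 = 9.1%, central 5,000/30,000 = 16.7%, high 7,200/38,800 = 18.6%.
- Adjusted: low 2,554/34,417 = 7.4%, central 3,556/28,000 = 12.7%, high 4,831/35,498 = 13.6%.

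| Variance saved by averaging | Low | Central | High |
|---|---|---|---|
| Mean of 13 counts, raw change | 11% | 24% | 28% |
| Mean of 13 counts, adjusted | 9% | 19% | 22% |
| Single visit, raw change | 9% | 17% | 19% |
| Single visit, adjusted | 7% | 13% | 14% |

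**Relaxing independence.** Let r0 be the correlation between screening and Day 0, and r that between either of them and one follow-up count, with equal variances. The saving is (1 − r0)/(4(1 − r)) for raw change and r²(1 − r0)/((1 + r0)(1 − r²)) after adjustment.

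- r0 = 0.8, r = 0.6: 0.2/1.6 = 12.5% raw; 0.072/1.152 = 6% adjusted.
- r0 = 0.95, r = 0.7: 0.05/1.2 = 4% raw; 0.0245/0.9945 = 2.5% adjusted.

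In these cases averaging still helps, but the gain can become small.

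**The case against.** Several points on the other side have force.

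*Day 0 alone is not stated text.* A reader might infer that the plan expressly restricts the baseline to Day 0. It does not: that follows from a visit label. The protocol also uses the word more loosely. Section 6.5 says cardiovascular risk factors "will be evaluated at baseline and annually during the trial", while the schedule puts the pre-treatment risk assessment, lipids and glucose at screening. This stands. It lowers the claim to a natural reading, and it is also a reason to write the definition down.

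*The size is assumed.* A reader might take the percentages as a property of this trial, or convert the central case into about 32% more patients (1/(1 − 0.241) = 1.32). The documents support neither. No CD4 variability is given, no precision target for CD4 is set or missed, and the follow-up summary (one visit or a mean over visits) is left open. The upper figures need the 13-count mean. Counts weeks apart may well be more alike than counts years apart, which shrinks the gain.

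*Baseline adjustment could do the job instead.* Only in part. The adjusted rows of the table still show a saving, and the plan does not say that it will adjust.

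*The screening count is selected.* Entry requires more than 100 cells/mm³ at screening. That selection precedes randomisation and applies to both arms alike, so it does not bias the comparison.

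*Details are deferred, and a Day 0 baseline is ordinary practice.* Both are true. Nothing in the plan is invalid; this is an improvement to adopt while the full analysis plan is still to be written.

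**Conclusion.** The point holds as a free gain in precision on one secondary outcome. Two pre-switch counts are held, the natural reading uses one, and averaging them lowers the variance without biasing the comparison. Under the assumed SDs and independent within-patient variation, the reduction is about 11% to 28% (raw) or 9% to 22% (adjusted) for a mean over 13 counts, and about 9% to 19% or 7% to 14% at a single visit. It can fall to a few per cent if the two early counts are much more strongly correlated with each other than with later ones. The direction is well supported; the size is not known from the documents. The primary analysis and the sample size are untouched.

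**What to change.** In section 9.2.2 and the full statistical analysis plan, define baseline CD4 as the mean of the screening and Day 0 counts, or the available one if the other is missing. Use that value in the repeated-measures analysis of section 9.5.2, and state there whether the model also adjusts for it. The cost is a line or two of text, settled before the data are analysed. No extra visit, blood sample or data collection is needed.
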